# NATIONAL APPLICATION FORM FOR ETHICAL APPROVAL OF A RESEARCH PROJECT

NAF-2009-v1

The application guidelines (NAFG-2009-v1) are to be read before completing this form to ensure that the questions are answered appropriately.

The electronic version of this form is formatted the same way as the paper version so that, for example, where an answer needs six lines, six lines are formatted, but where an answer only needs one line, one line is formatted. Please note the number of lines allowed for a question before answering it and make sure that you do not use extra lines.

You may find it helpful to print out the application form before completing it to help you to keep to the page limits allowed. **No extra pages should be added,** except where specified, as appendices.

The relevant paragraphs of the Operational Standard for Ethics Committees (Ministry of Health document) have been included in subject headings for reference.

The page breaks are not to be deleted as this will affect the formatting of the form.

When collating your application, please ensure that the information sheet, consent form and any attachments are placed behind the application form before copying. Applications not correctly collated, ie not in complete sets ready to be sent to committee members will be returned.

**Do not include this page with your application.**

# Checklist for Applicants – attach to front of application

**Before sending your application form, please check to make sure that all relevant information has been attached. If not applicable to the application write N/A. Protocols, information sheets, consent forms, questionnaires, advertisements, letters of invitation, data collection or other study forms must have a version number and date (marked *).**

**Please note: Incomplete applications will not be considered. Pending is an option only for written confirmation of Maori consultation, SCOTT approval, and Locality assessment by organisation. For multi-region studies, the documentation for one site must be complete.**

| **Reference** | **Item** | **Yes, pending or N/A** |
| --- | --- | --- |
| Observational Studies Guidelines 5.11 | * Study protocol – must be supplied with all applications | Yes |
| Page 21 of NAFG, QE on NAF | * Consent form | Yes |
| Page 23 of NAFG, QE on NAF | *Information sheet | Yes |
| QA5.4 on NAF | * Questionnaire/interview guidelines | Yes |
| Page 8 of NAFG, QA2 of NAF | Scientific assessment | Yes |
| QA5.3 of NAF | Statistical report | Yes |
| QD2, NAFG page 8 Q A4 | * Advertisement, letter of invitation | Yes |
| Section F of NAFG, Page 15 | Evidence of Māori consultation | Pending |
| Part 4 of NAF | Declaration signed by principal investigator, Head of Department or Dean (for each site) | Yes |
| Part 4, Form A or B of NAF | Accident compensation declaration correctly witnessed | N/A |
| NAFG page 20, NAF page 28 | Form/s for registered and unregistered medicines | N/A |
| Pages 11 and 35 (Appendix 1) of NAFG, QB17 on NAF | Standing Committee on Therapeutic Trials (SCOTT) approval attached if drug is unregistered in New Zealand | N/A |
| Locality assessments form(s) NAFG pages 18-20 | Completed by ethics committee if required, or completed by locality organisation(s) if received at time of submission | Pending |
| NAFG pages 30-32 | Part 5: If there any use of tissue (includes blood, saliva, skin) | Yes |
| Appendix 2 of NAFG | Part 6: If the research involves any gene or genetic studies | Yes |
| Appendix 2 of NAFG | Part 7 if the study involves xenotransplantation | N/A |
| NAFG pages 33-34 | Part 8 if any participants are unable to consent themselves including children | N/A |
| Parts 6 and 7, Appendix 2 of NAFG | GTAC approval if required | N/A |
| QB17 of NAF, Appendix 4 of NAFG | National Radiation Laboratory risk assessment if required | N/A |
| **Company sponsored studies** | Investigator brochure (if product is unregistered in New Zealand) | N/A |
|  | Signed indemnity agreement (sponsor/institution/investigator) |  |
|  | Current company insurance certificate |  |
| If yes to C.6 | Evidence of sponsor indemnity insurance to cover C.6 |  |
| If yes to C.6 | Evidence of hospital/institution indemnity insurance to cover C.6 |  |
| If yes to C.6 | Evidence of Investigator indemnity insurance to cover C.6 |  |

|  | | | | | | | | | | | | |  |
|  | | | | | | | | | | | | |  |
| 8. Where this is supervised work | | | | | | | | | | | | |  |
| 8.1 Supervisor’s name | | | | Not applicable | | | | | | | | |  |
| Position | | | |  | | | | | | | | |  |
| Daytime phone number | | | |  | | | | | | | | |  |
|  | | | | | | | | | | | | |  |
| 8.2 Signature of supervisor (where relevant)  Declaration: I take responsibility for all ethical aspects of the project | | | |  | | | | | | | | |  |
|  | | | | | | | | | | | | |  |
| 9. List locality organisation/s involved, including contact address, and complete the locality assessment in Part 4: Declarations (refer to the Guidelines (NAFG-2009-v1)) | | | | Christchurch Diabetes Centre, [name], Christchurch.  School of Sciences and Physical Education, University of Canterbury, [name], Christchurch. | | | | | | | | |  |
|  | | | | | | | | | | | | |  |
| 10. I wish the protocol to be heard in a closed meeting. | | | | | | | |  | Yes | X | | No |  |
|  | | | | | | | | | | | | |  |
| If the answer is yes, please provide a reason why you wish the protocol to be heard in a closed meeting in accordance with the Official Information Act 1982. | | | |  | | | | | | | | |  |
|  | | | | | | | | | | | | |  |
| 11. If the study is based, in part or in full, overseas, which countries are involved? | | | | Not applicable | | | | | | | | |  |
|  | | | | | | | | | | | | |  |
| 12. Has this application been reviewed by another ethics committee in New Zealand | | | | | | | |  | Yes | X | | No |  |
| or overseas? | | | | | | | | | | | | |  |
| (If yes, advise which country, the name of the committee/s and the decision/s of the committee/s)  Please note a copy of the report/s may be requested. | | | |  | | | | | | | | |  |
|  | | | | | | | | | | | | |  |
| 13. **Human tissue** – Does the project involve collection or use of human | | | | | | | | X | Yes |  | | No |  |
| tissue? If **yes**, complete Part 5. | | | | | | | | | | | | |  |
|  | | | | | | | | | | | | |  |
| 14. **Gene studies** – Does this research involve any gene or genetic studies? | | | | | | | |  | Yes | X | | No |  |
| If **yes**, complete Part 6. | | | | | | | | | | | | |  |
|  | | | | | | | | | | | | |  |
| 15. **Xenotransplantation** – Does this research involve the transplantation of | | | | | | | |  | Yes | X | | No |  |
| living biological material from one species to another? | | | | | | | | | | | | |  |
| If **yes**, complete Part 7. | | | | | | | | | | | | |  |
|  | | | | | | | | | | | | |  |
| 16. **Consent** – Are all participants able to provide consent for themselves? | | | | | | | | X | Yes |  | | No |  |
| If **no**, complete Part 8. | | | | | | | | | | | | |  |
|  | | | | | | | | | | | | |  |
| 17. **Lay summary** – give a brief **lay (non-technical)** summary of the study (not more than 200 words) such as you would give as an explanation to participants. | | | | | | | | | | | | |  |
|  | Traditionally low intensity “fat burning” endurance training (LIET), for example steady walking or jogging, has been prescribed for those at-risk of developing type 2 diabetes and cardiovascular disease (CVD). This type of exercise has resulted in some reduction of risk factors but limited exercise adherence success. Recent research suggests high intensity exercise (HIIT) or maximal volitional intensive training (MVIT), which is a form of interval training, may provide a time efficient method for improving risk factor reduction. This reduction in time input may help with exercise adherence. Much of the HIIT research has been based in the exercise laboratory. The study objective is to examine whether these findings can be translated to real world settings and populations at-risk of diabetes and cardiovascular disease, in a New Zealand context. In the first 12 week phase of the research translation, standard low intensity activity (LIET) will be compared to two high intensity programmes (HIIT and MVIT), in at-risk populations. In the second 6 month phase the high intensity exercise interventions will be adapted to match those readily available to participants in their local area. Changes in fitness and metabolic risk factors will be assessed along with exercise adherence. | | | | | | | | | | | |  |
|  | | | | | | | | | | | | |  |
| 18. Proposed starting date (dd/mm/yy) | | | | 01/02/2010 | | | | | | | | |  |
|  | | | | | | | | | | | | |  |
| 19. Proposed finishing date (dd/mm/yy) | | | | 30/07/2011 | | | | | | | | |  |
|  | | | | | | | | | | | | |  |
| 20. Duration of project in New Zealand (mm/yy) | | | | 18 months | | | | | | | | |  |
|  | | | | | | | | | | | | |  |
| 21. Proposed final report date (mm/yy) | | | | 01/12 | | | | | | | | |  |
|  | | | | | | | | | | | | |  |
| 22. Has the clinical trial been registered? | | | | | | | |  | Yes | X | | No |  |
|  | | | | | | | | | | | | |  |
| If **yes**, name the register. | | | |  | | | | | | | | |  |
|  | | | | | | | | | | | | |  |
| If **no**, has registration been applied for? | | | | | | | |  | Yes | X | | No |  |
|  | | | | | | | | | | | | |  |
|  | **Comment**: The investigators plan to register the study with the Australian New Zealand Clinical Trials registry, once Ethical approval has been obtained (ie following any suggested amendments from the Ethics Committee) | | | | | | | | | | | | |
|  | | | | | | | | | | | | |  |

# Part 2: Ethical Principles

## A. Validity of research *(Operational standard paragraphs 53–59)*

### Scientific basis

#### A1. Aims of the project

| A1.1 What is the hypothesis/research question(s) and/or the specific aims of the project? (State briefly.) | |
| --- | --- |
|  | **Comment**: This translational research project aims to assess whether the beneficial effects of high intensity exercise programmes seen in controlled settings e.g. the exercise laboratory, can be reproduced in a ‘real world’ New Zealand setting, in subjects at risk of diabetes and CV disease. VO2max is a positive predictor of beneficial health outcomes,1 and change in VO2max after exercise will be used as the primary endpoint.  The study will be undertaken in two phases. Both phases will follow standard RCT design. Phase 1 is predominantly an efficacy study, aimed to test the hypothesis that high intensity activity produces results that are superior to that of a standard walking programme. Subjects at risk of diabetes and cardiovascular disease will be recruited from the community, by advertisement. They will be randomised to one of the following: control intervention (LIIT) ie the usual exercise ‘prescription’ and two comparator exercise interventions, high (HIIT) intensity activity or maximal volitional intensity training (MVIT) ie interval training. Phase 2 is predominantly an effectiveness study. The most effective high intensity exercise prescription from Phase 1 will be compared with LIIT. Once again, the programme will be offered to subjects recruited from the community, by advertisement and also by word of mouth. Recruitment for Phase 2 will be weighted towards Maori participation. The primary outcome for both phases of the study is change in subjects’ fitness, as assessed by changes in VO2max. Changes in metabolic risk factors will be used as secondary outcomes.  *1. Kodama et al, Cardiorespiratory fitness as a quantitative predictor of all-cause mortality and cardiovascular events in healthy men and women: A meta-analysis. JAMA 2009: 301: 2024-2035.* |

#### A2. Scientific background of the research

| A2.1 Has this project been scientifically assessed by independent review? | | | X | Yes |  | No |
| --- | --- | --- | --- | --- | --- | --- |
|  | | | | | | |
| If **yes**, describe the process, for example, HRC funding assessment process. *A copy of the report should also be attached. The researcher’s response may also be included.* | | This project has been through the DHB/HRC scientific assessment process, as part of the DHB research fund: Translational research in CV diabetes, diabetes and obesity. See the following website for details, including funding details:  http://dhbrf.hrc.govt.nz/index.php/current_projects | | | | |
|  | | | | | | |
| If **no**, do you intend to have the project scientifically assessed and by whom? | |  | | | | |
|  | | | | | | |
| A2.2 Describe the scientific basis of the project **(300 words maximum**). Where this space is inadequate, continue on a separate sheet of paper. *Do not* delete page breaks or renumber pages. | | | | | | |
|  | Physical inactivity is endemic in developed societies and ‘lack of time’ is cited as a major contributor to inactivity (1, 2). The usual exercise prescription given for those with, or who are at-risk of, type 2 diabetes and cardiovascular disease is high volume low intensity endurance training (LIET). Recently low volume, high intensity interval training (HIIT) has been proposed as a more time efficient strategy for improving oxidative capacity and inducing metabolic adaptations equal to LIET. This approach has successfully been used with obese ‘middle aged’ individuals (3, 4). We will examine the health and exercise adherence benefits of HIIT or MVIT in comparison with LIET, in patients who are diagnosed with risk factors associated with the development of type 2 diabetes and CVD.  1. Blair SN. Physical inactivity: the biggest public health problem of the 21st century. BMJ. 2009;43(1):1-2.  *2. Godin GR, Desharnais P, Valois P, Lepage P, Jobin J, Bradet R. Differences in perceived barriers to exercise between high and low intenders: Observations among different populations. Am J Health Promot. 1994;8:279-85.*  *3. Tjonna AE, Lee SJ, Rognmo O, et al. Aerobic interval training versus continuous moderate exercise as a treatment for the metabolic syndrome: a pilot study. Circulation. 2008;118(4):346-54.*  *4. Wisloff U, Stoylen A, Loennechen JP, et al. Superior cardiovascular effect of aerobic interval training versus moderate continuous training in heart failure patients: a randomized study. Circulation. 2007;115(24):3086-94.* | | | | | |

#### A3. Study design

| A3.1 Describe the study design. Where this space is inadequate, continue on a separate sheet of paper. *Do not* delete page breaks or renumber pages. | |
| --- | --- |
|  | The study follows a randomised controlled trial (RCT) design and is divided into two Phases. Phase 1 is primarily an efficacy study, conducted over 12 weeks. This study will examine three exercise prescriptions (LIIT, MVIT, HIIT). Phase 2 is an effectiveness study, will be weighted towards Maori participation and will be conducted over 6 months. The exercise prescriptions used in Phase 2 will be the most successful high prescription from Phase 1 (ie either MVIT or HIIT), compared to a standard low intensity walking programme (LIIT) .The exercise prescription for the LIIT, MVIT and HIIT will be isocaloric ie those taking part in the high intensity arm of the programme will spend less overall time undertaking their exercise programme. Participants will have an elevated BMI and will not be regular exercisers. Participants will be asked to follow an exercise prescription as part of the study but will not be asked to change their diet. Participants must be physically well enough to able to undertake walking as their main form of exercise. Each phase will have separate participants.  All three of the exercise interventions will have a walking based component. They will be conducted by exercise leaders, trained to undertake the relevant exercise programmes in a standardised manner. (These exercise leaders will be provided by CPIT and are likely to include applied exercise physiology students undertaken a supervised Practicum). The exact intensity of exercise will however be individualised ie based on the subject’s pre-study fitness levels and performance when undertaking maximal volitional exercise. Fitness will improve during the study, thus exercise load will increase as the study progresses. Some subjects in the high intensity arm may therefore be considered ‘fit’ enough to incorporate a light jogging component to their exercise plan.  Data collection for Phase 1 will be undertaken before and after the twelve week intervention period. The same data will be collected for Phase 2 but will be collected at three time points: week 0, week 13 and week 26. Data will include a standardised exercise/fitness assessment, measuring V02 max on a treadmill test, standard anthropomorphic measurements, including waist circumference and an impedance measurement of total body fat, fasting venous blood collection for measurement of insulin, glucose, lipids and HsCRP. Subjects will complete several validated questionnaires including a four day food diary (to assess the extent that change in diet might act as a confounder) and quality of life assessments. The exercise physiology researchers undertaking the primary outcome measurement (VO2 max), will be blinded to group allocation.  Trial conduct, including the reporting of subject enrolment and follow up, will be undertaken using the CONSORT (Consolidated Standards of Reporting Trials) framework.  In summary phase 1 will look to use the positive results found in laboratory based heavily structured and tightly monitored exercise interventions and transfer these positive results to more community-based, less structured but still tightly controlled exercise intervention. In Phase 2 of the study we want to use the results found in phase 1 and apply them to an even less-structured, less tightly controlled but more realistic and much less expensive community-based exercise intervention.  (see Appendix 1 on separate sheet for more detail). |

#### A4. Participants

| A4.1 How many participants do you intend to recruit? (Include details for each locality organisation.) | |
| --- | --- |
|  | Phase 1;- 60 participants, anticipating that 48 will complete the study (16 in each arm).  Phase 2;- This less structured community based phase of the study is likely to experience a higher ‘drop out’ rate. 60 participants will be recruited, anticipating that 44 participants will complete the study (22 in each arm). |
|  | |
| A4.2 Give a justification for the number of research participants proposed, giving the details of power calculations when appropriate. | |
|  | A sample size of 16 in each group for the first study, will enable effect sizes >1.0 to be detected as statistically significant (two tailed-alpha=0.05) with 80% power. Assuming an untrained VO2 max of 30 ± 4ml/kg/min, this equates to differences in changes in VO2 max over 12 weeks of approximately 4 ml/kg/min.  A sample size of 22 per group in the second study will enable effect sizes >0.9 to be detected as statistically significant (two tailed-alpha=0.05) with 80% power, this equates to differences in changes in VO2max over 26 weeks of approximately 3.5ml/kg/min.  (To place this in context, a sedentary individual typically has a VO2 max of 25-35ml/kg/min +/- SD of 4 and a trained adult has a VO2 max around 40-60 ml/kg/min). |
|  | |
| A4.3 If randomisation is used, explain how this will be done. | |
|  | After consenting and baseline measurements, subjects will be randomly allocated in a 1:1:1 ratio to the exercise interventions, under the supervision of the medical biostatistician (CF).For both studies it is important to achieve a balance in gender and this will be achieved by stratified randomisation. |
|  | |

#### A5. Statistical method

| A5.1 Is the method of analysis quantitative? | | | X | Yes |  | No |
| --- | --- | --- | --- | --- | --- | --- |
|  | | | | | | |
| Or qualitative? | | |  | Yes | X | No |
|  | | | | | | |
| If the method of analysis is **wholly qualitative**, go to question A5.4. If the method of analysis is **wholly or partly quantitative**, complete the following: | | | | | | |
|  | | | | | | |
| A5.2 Describe the statistical method that will be used to analyse the data. | | | | | | |
|  | Initial data analysis will be conducted by [name] and colleagues using the Statistical Package for the Social Sciences (SPSS) software programme. Final data analysis will be undertaken under the supervision of Associate [name], medical biostatistician. For both studies changes in continuous outcome measures (e.g. VO2max, BMI, etc) will be compared between groups using ANCOVA. These models will utilise the stratification variable, gender, as a factor and the baseline measure as a covariate. The appropriateness of these parametric analyses will be confirmed by visual inspection of the residual plots. If these do not confirm normality, data maybe transformed prior to analyses and if this does not remedy problems then non-parametric analyses will be undertaken. A two-tailed p value of <0.05 will be taken to indicate statistical significance.  The primary outcome measure is change in VO2max.  The secondary outcome measures are changes in: BMI, waist circumference, blood pressure, insulin sensitivity (HOMA) and lipids.  Tertiary outcome measures are changes in: % body fat as measured by bioimpedance, Quality of Life, hs CRP.  Samples will also be collected for an exploratory study measuring changes in a novel marker of muscular ‘fitness’, namely monocyte mitochondrial load. | | | | | |
|  | | | | | | |
| A5.3 Has specialist statistical advice been obtained about this study? | | | X | Yes |  | No |
|  | | | | | | |
| If **yes**, from whom? (A brief statistical report should be included if appropriate.) | | Associate [name], University of Otago. | | | | |
|  | | | | | | |
| A5.4 If the method of analysis is **wholly or partly qualitative**, specify the method. Why is this method appropriate? If interviews are to be used, include the general areas around which they will be based and a copy of the interview guide, if one is to be used. Copies of any questionnaires that will be used must be included. | | | | | | |
|  | Not applicable | | | | | |

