**Phase 2**

In phase two, results from phase one will be used to fine-tune the testing and training protocols. In this phase 44 new to the study participants will be randomly assigned into 2 groups; the best high intensity programme from Phase (ie HIIT or MVIT) and a control group undertaking LIET. There will be 22 participants in each group. Subjects will undertake blood testing and VO2 max as for Phase one at times 0, 13 and 26 weeks. The second VO2max test done at 13 weeks will be used to check progress and adjust the training intensities for the final 3 months of training. Once a week each exercise group will come together at a local venue (Halswell Health Medical Centre or the Whanau Tautoko Charitable Trust) where instructors (trained undergraduates from CPIT, Canterbury or Lincoln University who will all have current First Aid qualifications) will take the group through their training for that day. The other two exercise sessions each week will take place at a venue chosen by the individual participants, either at the participant’s home or in a convenient community location. All participants will exercise with the aid of a heart rate monitor thereby allowing the participants to control their corresponding exercise heart rate relative to VO2peak. The instructors will monitor each participant’s heart rate each week to ensure training sessions are carried out in the desired heart rate throughout the 6 month training period

See next page for the testing protocols.

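### The Phase 2 model in A5.2 makes no use of the week-13 result for participants lost before week 26; a repeated-measures model would use it, for a modest gain

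*Protocol*

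**What the plan says.** Section A5.2 gives one model for both phases: "For both studies changes in continuous outcome measures (e.g. VO2max, BMI, etc) will be compared between groups using ANCOVA". It then names the terms: "These models will utilise the stratification variable, gender, as a factor and the baseline measure as a covariate". No visit term, within-person covariance or week-13 term appears. The endpoint is given without a visit: "The primary outcome measure is change in VO2max".

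Section A3.1 sets the Phase 2 schedule: "The same data will be collected for Phase 2 but will be collected at three time points: week 0, week 13 and week 26". Appendix 1 (Phase 2) repeats it for the primary outcome: "Subjects will undertake blood testing and VO2 max as for Phase one at times 0, 13 and 26 weeks". The one use that it states for the middle treadmill test is operational: it "will be used to check progress and adjust the training intensities for the final 3 months of training".

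Section A4.1 recruits 60 to Phase 2, expects 44 to complete (22 per arm), and anticipates more drop-out than in Phase 1. Section A4.2 sizes Phase 2 on the difference in change over 26 weeks: 22 per group, effect size above 0.9, about 3.5 ml/kg/min, two-sided 5% level, 80% power.

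**The concern.** The stated model suits Phase 1, which has one measurement after baseline. Phase 2 has two. In a week-26 ANCOVA without imputation, a participant tested at weeks 0 and 13 but not at week 26 adds nothing to the primary comparison. Yet the week-13 value is the most recent measured response, and is likely to be the best predictor of the missing one.

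Two things are at stake. One is some precision, in a phase where the protocol itself expects about a quarter of participants to be lost. The other is protection against bias, should those who stop in the second half of one arm be people who had responded poorly by week 13. The values are already collected under the plan, so the question is only which model is fitted.

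**Working it through.** **1. The plan's own figures.** Inputs from A4.1 and A4.2: 22 per arm, SD 4, difference 3.5 ml/kg/min, two-sided 5%.
- Standardised effect: 3.5/4 = 0.875, which the protocol rounds up to 0.9.
- A two-sample t-test at 0.875 needs 22 per group and has 80.9% power (82.7% by the normal approximation). The stated 22 is reproduced.
- Loss: 16/60 = 26.7%, or 8 per arm with 30 randomised per arm; 44/(1 − 16/60) = 60.

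**2. Precision if late losses are random.** Let n13 be the number per arm with a week-13 value, and r the correlation of the week-13 and week-26 values given baseline. The protocol gives neither, so both are assumptions. With 22 per arm observed at week 26, a likelihood analysis of both visits gives

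variance of an arm mean at week 26 = SD² × [(1 − r²)/22 + r²/n13],

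so the proportional reduction against completers only is r² × (1 − 22/n13).

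| Lost after week 13, per arm | n13 | Reduction, r = 0.5 | Reduction, r = 0.8 | Effective n per arm |
|---|---|---|---|---|
| 0 | 22 | 0% | 0% | 22.0 |
| 2 | 24 | 2.1% | 5.3% | 22.5 to 23.2 |
| 4 | 26 | 3.8% | 9.8% | 22.9 to 24.4 |
| 8 (all) | 30 | 6.7% | 17.1% | 23.6 to 26.5 |

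Worked case: assume correlations of 0.80 (weeks 0 and 13), 0.85 (13 and 26) and 0.75 (0 and 26).
- r = (0.85 − 0.80 × 0.75)/√[(1 − 0.80²)(1 − 0.75²)] = 0.25/0.397 = 0.63, so r² = 0.397.
- Four late losses per arm: 0.397 × (1 − 22/26) = 6.1%.
- Six late losses per arm: 0.397 × (1 − 22/28) = 8.5%.
- Simulation of 4,000 trials per setting gave 5-9%, worth one to two completers per arm.

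**3. No late losses.** When everyone with a week-13 value also has a week-26 value, the two estimates coincide (largest simulated difference about 1e-13). The week-13 data then add nothing to the week-26 contrast.

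**4. Loss that depends on week-13 response.** Same assumed correlations, SD 4, 30 randomised and 8 lost per arm, 4 to 6 of them after week 13.
- Low week-13 gainers leave the high-intensity arm only, strong selection: completer ANCOVA overstates the contrast by 0.37 to 0.48 ml/kg/min (0.37/3.5 = 11%; 0.48/3.5 = 14%). Its two-sided type I error is about 7.5-9%.
- Weaker one-arm selection, with noise twice the signal: bias about 0.2 to 0.26.
- The lowest gainers always leave that arm, the extreme case: bias 0.45 (4 late losses) or 0.57 (6).
- Like selection in both arms: bias about zero.
- The estimate that uses week 13 has bias of about zero throughout. That follows from the set-up, in which loss depends only on observed values.

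**The case against.** The strongest reply is that nothing here is an error. ANCOVA of the 26-week change, with baseline and the stratification factor, is a standard and valid analysis, and A4.2 ties Phase 2 to 26 weeks. That stands: the point is about a better use of the data.

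A reader might infer that the protocol excludes week-13 outcomes from analysis. It does not say so. Appendix 1 gives one use of the middle test without calling it the only one, and the protocol is silent on imputation. The omission is read from the listed terms and goes no further than that.

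It can also be said that visit structure and missing-data handling belong in a statistical analysis plan, which was not available. In part that is right. But A5.2 is not silent: it names a model and its covariates for both phases, so a later plan must either inherit that model or depart from it.

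On size, the objection has force. With the assumed 0.75 correlation between weeks 0 and 26, the ANCOVA residual SD is 4 × √(1 − 0.75²) = 2.65, and 22 per arm already gives about 99% power for 3.5 ml/kg/min. A 5-9% fall in variance would then hardly affect power. Nor does anything in the protocol indicate that poor responders would leave one arm only.

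Finally, a reader might infer that weeks 13 and 26 will both be tested as primary, with an inflated false-positive rate. The protocol plans no such pair of tests, and its 26-week sample-size basis argues against it.

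**Conclusion.** The point holds as a recommendation to improve the method, not as an invalid analysis. A5.2 carries a one-follow-up model into a phase with two follow-ups and an expected loss of 16 in 60. Read as a week-26 ANCOVA, it cannot draw on the week-13 results of people lost later.

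The expected gain is modest: about 5-9% of variance if 4 to 6 per arm are lost at random after week 13, and none if no one is. The better reason for the change is protection. If loss depended on observed week-13 response differently by arm, completer ANCOVA could be off by roughly 0.2-0.5 ml/kg/min, and a repeated-measures model would remove that. A reader might take the 11-14% overstatement and the 7.5-9% type I error as what will happen. They illustrate strong selection in one arm and are not expected consequences. Neither method is protected if loss depends on later values that were never observed.

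All of this rests on assumed correlations and timing of losses, and on A4.1's 60 recruited. Appendix 1 instead has 44 assigned to two groups of 22; the two passages should be reconciled.

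**What to change.** In A5.2, keep ANCOVA for Phase 1. For Phase 2, specify a mixed model for repeated measures on the week-13 and week-26 values:
- terms for arm, week, arm × week, baseline × week and gender;
- unstructured within-person covariance;
- all randomised participants with any follow-up value;
- the arm contrast at week 26 as the single primary test, with week 13 as supportive.

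The cost is a sentence or two of text and slightly more modelling, within the SPSS software already named. No extra visit, participant or measurement is needed, and with complete data the answer is essentially that of the planned ANCOVA. The model relies on data being missing at random given the observed values, and the plan should state that assumption.
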